## Discussion

This study is a randomized controlled clinical trial with the grouping comparison of FC, FG, and FCF. To our knowledge, so far, this study may be the first clinical trial study that aims to demonstrate the FC effect on AHZ infection with rigorous design and it may also be different from the reference therapy. However, it has gotten our attention that several existing Chinese literatures did report on fire needle and cupping technique to cure for HZ [12–14, 16] but all of them did not take up a rigorous design trial and are lacking of sufficient evidence to prove FC treatment has a positive effect on AHZ.

The key objective of this study is to test the three designed treatment groups on the analgesic effect in acute phase of AHZ disease. We will also pay great attention to the observation of the scores of skin lesions, since skin rash is also the deep concern of patients. We also want to detect variation in serum due to the fact that the substance P and ®-Ep are often regarded as the analgesic mechanism. In addition, the occurrence of postherpetic neuralgia may need to be carefully observed and examined due to its common occurrence and hard to cure nature in AHZ infection. The symptom of acute pain is what the AHZ patients want to solve mostly and cannot approve to participate in an invalid treatment group.

This study is intended to design a rigorous trial protocol that will yield evidence on effective acupuncture technique. In that, this study should be closer enough to the clinical real-world research. Nevertheless, there are confounding factors associated with this designed trial that cannot be completely avoided. First, there is no separate set of sham acupuncture as a control group for FC treatment. Since the first group of FC treatment is already a combination of two types of acupuncture techniques, it is hard to implement another set of sham acupuncture. Another issue of the ethical principle will also make it difficult to perform sham acupuncture for FC treatment since conflicts of interests may happen for patients who have already suffered from severe pain and will not be likely to accept sham acupuncture. Note that, however, the psychological effects cannot be ruled out for lack of sham acupuncture group [17–19]. Second, the blind method is also impossible to perform under the current designed trial since it is not possible for acupuncturists and subjects to do so under the operation of FC treatment. Instead of blinding, the FG and FCF treatments have both been designed to set as the control interventions. As such, the results from FG would be good enough to give evidence of comparison and FCF is also a good way to show whether the combination of drug with FC treatment will yield a better result than the FC treatment alone. Third, as in our clinical practice, acute pain associated with AHZ infection tends to be amplified alongside with the development of the AHZ disease. Therefore, as an intra-trial arrangement, the temporary short-acting painkillers will be permitted to all the selected patients regardless of their group divisions. Having such intra-trial, temporary, and low dose pain release drugs will have no obvious effect on the results. Another limitation of this trial is the psychological factors that cannot be eliminated according to the present design, and the difference in immunity is relative to the recovery of HZ which may lead to differences in prognosis. Finally, according to the actual clinical situation, the drug dose, as well as the number of FC treatment interventions, has certain volatility and does not restrict sternly.

In all, this protocol will act to provide a reference of clinical methodology and may give definite evidence on the effect of FC intervention for AHZ as it is designed.

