### Intervention

#### Group A

This group will be treated with only FC.
Acupoints: the main points are Ashi points (lesion area), corresponding nerve segment Jiaji points, and branch ditch points (SJ6); matching points are selected according to syndrome differentiation, pattern of dampness-heat in the liver meridian with Yang Ling Quan (GB34), pattern of dampness-heat in the spleen meridian with Yin Ling Quan (SP9), and pattern of obstruction of collaterals by blood stasis with blood sea (SP10).Appliances: medium-sized fire needle (diameter 0.4 mm), large-sized fire needle (diameter 0.65 mm), glass fire cup no. 1–5, medical cotton ball, alcohol lamp, lighter, iodophor, etc.Operational methods: routine disinfection of the skin with iodophor with the order of the head, middle, and tail of herpes will be carried out firstly. Holding 95% alcohol lamp by the left hand close to the needle, and to burn the needle in the right hand to whitening by the external flame of the fire, acupuncturist will prick the head of the herpes cluster. Then, the needles will be pricked into the blisters or rashes quickly from the surface of the skin to the base of the herpes. Pricking early-onset herpes at first, for larger pustules or blood blisters (diameter ε0.5 cm) with a large-scale fire, acupuncturist will extrude blister fluid with disinfection cotton ball after puncture, and then cup with a suitable size of glass fire cup for 5–10 min. If the area of the herpes cluster is too large, more than one cup can be used. The remaining acupuncture points are treated with fire needle pricking, and each acupuncture point should be pricked three times. Finally, the skin should be sterilized with iodophor more than one time. The treatment should be performed once a day for a total of 7 days.Skin care: after treatment, the iodophor is used to clean and disinfect the skin and to keep the patient’s skin dry and clean during the treatment.Course of treatment: the course of treatment is 1 week and from one to seven times. If there is no pain any more after one time of FC treatment, the course is just one time. Meanwhile, if the patient is still suffering pain, the FC will continue once a day unless the pain disappears. All the treatments will not be more than seven times no matter the pain or not.

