#### Temporary analgesics

If the patients in the three groups still cannot endure the pain during the treatment or after 1 week treatment, and for all patients who have difficulties to endure pain during the trial, as an intra-trial arrangement, temporarily analgesic medicine will be given to those in need with careful observation. According to the recommendations of the World Health Organization, all three groups are likely to receive standardized analgesic treatment as follows: step 1—non-opioid analgesics (paracetamol 4·1.0 g), 60 mmδ VASδ 50 mm; step 2—moderate-strength opioids (tramadol tablets, maximum dose 600 mg/day), 80 mmδ VASδ 70 mm; step 3—moderate-strength opioids (tramadol injection, 0.1 g, once a day), VAS = 90 mm; and step 4—recommend the use of stronger opioids (dezocine injection, 5 mg, once a day), VAS = 100 mm. Patients are forbad to use other analgesic drugs or therapies. Temporary analgesic demand will be recorded (Table 2).

**Table 2 Tab2:** Secondary outcomes

**Symptom or sign (points)**	0	1		2		3	
Pain intensity	No	Mild		Medium, tolerable		Severe, unbearable	
Local itching	No	Mild		Medium, tolerable		Severe, unbearable	
Burning sensation	No	Mild		Medium, tolerable		Severe, unbearable	
Rash color	No	Light red		Red, no edema		Red, edema	
No. of blisters	No	1–10		11–15		> 26	
Blister clusters	No	1–2		3–4		4–5	
Ulcer	No	Epidermis		Superficial ulcer		Deep ulcer	
Fever	No	≤ 38 °C		≤ 39 °C		> 39 °C	
Local lymphadenopathy	No	< 0.5 cm		0.5–1 cm		> 1 cm	
Rash area reduction percentage	0	< 30%		< 60%		100%	
**Analgesic demand (day)**	**1**	**2**	**3**	**4**	**5**	**6**	**7**
Paracetamol (g)							
Tramadol (mg)							
Tramadol injection (g)							
Dezocineinjection (mg)							

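### The Discussion says without support that rescue analgesia will not noticeably affect the results; separately, the rescue ladder leaves gaps on the stated millimetre scale

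*Protocol article*

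**What the plan says.** The Discussion introduces its limitations by saying that "there are confounding factors associated with this designed trial that cannot be completely avoided". The third is rescue medication: "the temporary short-acting painkillers will be permitted to all the selected patients regardless of their group divisions". It then concludes: "Having such intra-trial, temporary, and low dose pain release drugs will have no obvious effect on the results".

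The Temporary analgesics section gives the rule. Rescue is for patients in any group who "still cannot endure the pain during the treatment or after 1 week treatment". The ladder has four steps:

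- VAS 50–60 mm: paracetamol 4 × 1.0 g.
- VAS 70–80 mm: oral tramadol ("tramadol tablets, maximum dose 600 mg/day").
- VAS exactly 90 mm: tramadol injection 0.1 g once a day.
- VAS exactly 100 mm: "recommend the use of stronger opioids (dezocine injection, 5 mg, once a day), VAS = 100 mm".

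Other analgesic drugs or therapies are forbidden. Rescue use is recorded daily, by drug and day (Study design; Table 2), and the abstract lists analgesic need among the secondary outcomes.

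The primary outcome is the change in VAS (0–100 mm) from before to after treatment. Eligibility requires a VAS of 50–80 mm. The trial is described as open. Gabapentin is scheduled in group B only (Table 1).

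**The concern.** Rescue analgesics act on the quantity that the primary outcome measures. A rule that permits them equally in all arms does not make their use equal. Patients know their arm, rescue follows their own report that pain cannot be endured, and one arm of three already receives a scheduled analgesic drug. If use differs, the VAS contrast compares treatment plus one amount of rescue with treatment plus another. That comparison can be legitimate, but only if readers are told to interpret it that way. The printed assurance tells them the reverse.

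The ladder raises a separate, practical matter. On a millimetre scale, a patient with unendurable pain at 65 mm falls between steps 1 and 2 and may not be given anything else. Sites would have to improvise, and rescue would then be less uniform than the protocol intends.

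**Working it through.** **Is there a figure to reproduce?** The document gives none for rescue: no expected rate, no effect on VAS and no VAS standard deviation. Its sample size rests on cure rates and does not involve rescue. It does reproduce: with λ = 12.654 (chi-square, 2 df, α = 0.05, power 0.90), n = 2 × 12.654 / (2·asin√0.80 − 2·asin√0.378)² = 31.95, so 32 per group. Nothing below changes it.

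**The assurance against the rest of the protocol**

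1. *Dose.* The Discussion calls the rescue drugs low dose. The ladder allows tramadol tablets to 600 mg/day and describes its fourth step as stronger opioids. The 600 mg is a ceiling, not the dose each patient will take, but nothing in the section restricts rescue to low doses.
2. *Likelihood of use.* Everyone enters at 50–80 mm, the span of steps 1 and 2. The Discussion itself expects pain to increase as the disease develops. Steps 1 and 2 apply only when pain cannot be endured, so this shows that rescue is foreseeable, not how common it will be.
3. *Balance.* Group B has gabapentin, starting at 300 mg on day 1 and reaching 900 mg/day on day 3 (Table 1). Groups A and C have no scheduled analgesic drug. Greater rescue use in either direction is plausible.
4. *Analysis.* Rescue given under the ladder is part of the protocol, so it does not meet the dropout criterion about drugs outside the protocol, and the per-protocol set does not remove rescue users on that ground. The Statistical analysis section does not mention rescue. A separate analysis plan may do so, but nothing printed here supports the claim of no noticeable effect.

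**Labelled illustration, on assumed figures.** Per arm: 105/3 = 35. If one arm has k more patients than another whose final VAS is lowered by d mm through rescue, the contrast shifts by k × d/35.

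| k (assumed) | d (assumed) | Shift |
|---|---|---|
| 0 | any | 0 mm |
| 1 | 10 mm | 10/35 = 0.29 mm |
| 1 | 20 mm | 20/35 = 0.57 mm |
| 1 | 30 mm | 30/35 = 0.86 mm |
| 5 | 20 mm | 100/35 = 2.9 mm |
| 10 | 30 mm | 300/35 = 8.6 mm |

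The sign depends on which arm uses more. The last row combines the largest value assumed for each input. The table shows how the shift scales; it does not estimate one.

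**The ladder.** The inequality signs are damaged in the text, so the bounds are taken as inclusive, which is the reading most favourable to the protocol.

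- Whole millimetres from 50 to 100: 51 values. Covered: 50–60 (11) + 70–80 (11) + 90 (1) + 100 (1) = 24. Not covered: 51 − 24 = 27, namely 61–69, 81–89 and 91–99 (9 each).
- Within the eligible range 50–80: 31 values, 22 covered, 9 not covered (61–69).
- In 10-mm marks (50, 60, 70, 80, 90, 100): all 6 covered.

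These are counts of scale values, not of patients.

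**The case against.** The strongest reply is that this is one Discussion sentence that fixes no procedure or analysis. It stands in a list of acknowledged limitations. Rescue follows one ladder for all arms, is recorded daily, and counts as a secondary outcome, so use by arm can be reported in any case. Comparing arms regardless of rescue suits a trial that wants to stay close to practice. All of that stands, and it is why the primary analysis need not change. It does not support the sentence itself: recording a confounder is no evidence that it is harmless.

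On the ladder, every printed bound is a multiple of 10, and exact triggers at 90 and 100 mm make most sense if VAS is read in 10-mm marks. That may well be what was meant. The protocol nevertheless defines the scale as 0–100 mm and does not state such a rule.

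A reader might infer more than the document supports:

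- *That no rescue-free interval precedes the final VAS.* The article's text shows none, but the two schedule figures are not available and a full protocol exists. Its absence cannot be established.
- *That rescue would cut short fire needle treatment.* The Group A section says "the course of treatment is 1 week and from one to seven times" and "if the patient is still suffering pain, the FC will continue once a day unless the pain disappears". For rescue to withhold sessions, it would have to turn unendurable pain into no pain, and that would have to be taken as ending the course. The document gives no basis for expecting this.
- *That the VAS contrast is biased by a known amount.* The illustrative shifts rest wholly on assumed inputs and include zero.
- *That excluding prior painkiller use contradicts permitting rescue.* That criterion secures a clean baseline and is compatible with rescue afterwards.

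**Conclusion.** The concern holds in two limited parts. First, the assurance about rescue is unsupported, and its low-dose description does not match the permitted ladder. Because the primary outcome is pain, the trial is open and scheduled analgesia is given in one arm only, an effect on the VAS contrast cannot be ruled out; its size and direction cannot be stated from the document. Second, the ladder leaves 27 of 51 whole-millimetre values without a step (9 of 31 in the eligible range) if VAS is read to the millimetre, and none if it is read in 10-mm marks. Both should be corrected. Neither affects the sample size, and neither shows that the trial's result will be biased.

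**What to change.** 1. Replace the assurance in the Discussion with a statement that the effect of rescue on the VAS contrast is unknown, and remove the low-dose description.
2. Keep the primary analysis regardless of rescue. Report rescue use by arm, from the existing daily record, beside the primary VAS result.
3. Add dose time and pre-dose VAS to the Table 2 rescue record. The ladder already implies that a VAS is taken before rescue, but neither field is printed.
4. Pre-specify one sensitivity analysis for patients whose final VAS falls within a set time after rescue, with the window fixed per drug before outcome data are seen; this may sit in the analysis plan. If the pre-rescue VAS is substituted, say that it is taken at peak pain and may over-penalise the arm that uses more rescue.
5. Make the ladder contiguous, with cut-points set by the clinical team, or state that VAS is read in 10-mm steps.

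The cost is two extra fields on a record already kept, one extra analysis, a clarified ladder and a more qualified headline result.

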### Trial status

This trial protocol is version 2.1, dated 24 April 2019. The trial recruitment will be on 10 October 2019, and recruitment will be completed about on 10 October 2020.

## Data Availability

The full protocol will be available from the corresponding author after identification. Datasets generated or analyzed during the study will not be made public until they are published in a peer-reviewed international journal.

## Abbreviations

HZ: Herpes zoster
AHZ: Acute herpes zoster
RCT: Randomized controlled trial
®-Ep: β-Endorphin
VAS: Visual analogue scale
FC: Fire needle + cupping
FG: Famciclovir + gabapentin
FCF: Fire needle + cupping + famciclovir
TCM: Traditional Chinese medicine
